### 5.2.2.2 Exposure: level of certainty for maternal immunisation

The applicability of the GAIA definition for maternal immunization will be assessed by calculating the proportion of vaccination mothers identified that can be classified according to the GAIA definition.

The denominator will be the number of vaccination mothers identified; the numerator will be the number of vaccination mothers identified that can be classified according to the GAIA definition.

The applicability of the GAIA definition will be reported overall, and stratified by site/country/region, by health facility level (primary/secondary/tertiary) and by type of data (paper vs. electronic).

The proportion of all mothers whose maternal vaccination status was assessed as exposed, non-exposed and unknown will be described.

## 5.3 Secondary study outcomes

### 5.3.1 Secondary study outcome 1 – Proportion of cases classified by level

#### 5.3.1.1 Health outcomes

For each health outcome, the proportion of cases that can be classified according to each GAIA case definition level will be assessed.

*Proportion of cases identified that can be classified by level*

- For each health outcome, the proportion of cases identified that can be classified according to each GAIA case definition level will be assessed.

---

 In this document, 'classified' will mean 'classified according to the GAIA case definitions'

- The denominator will be the number of cases *identified* for one outcome; the numerator will be the number of classified cases for each level of the GAIA case definition.

*Proportion of cases classified by level*

- For each health outcome, the proportion of cases classified by level will be calculated.
- The denominator will be the number of cases *classified* for one outcome for all levels; the numerator will be the number of classified cases for each level of the GAIA case definition.

These proportions will be reported overall, and stratified by site/country/region, and by health facility level (primary/secondary/tertiary).

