#### 4.7 Case identification and vaccine exposure assessment

Identified cases are defined as children delivered at the site with a diagnosis of one of the health outcomes of interest at the same site. A list of potential cases will be drawn on a regular basis (e.g. weekly) from relevant data sources (see section 3.7).

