## 4.9 Data collection

Each delivery that takes place at the site will be registered and the occurrence of any outcomes of interest within 28 days of birth will be recorded in the electronic data capture system (EDC). In addition, the sex, birth weight, gestational age and the head circumference will be collected. From this, the total number of live births over one year and the total number of cases identified among those delivered at the site will be derived.

Once an outcome occurs and the inclusion and exclusion criteria are met (including informed consent), the infant enters the study. At each site, cases with outcomes of interest will be consecutively recruited into the study, until 100 cases for each outcome have been recruited, or the end of the study period is reached, whichever occurs first.

One infant may present with more than one outcome under study; cases will be recruited for all outcomes until 100 cases for each outcome has been reached. . Data on case ascertainment for each case and maternal vaccination status of the case's mother will be collected in an electronic CRF in an electronic data capture (EDC) system. CRFs are available in Annex 5. If necessary, a paper CRF may be used as an intermediary step.

The EDC system will generate a unique ID for each child. Forms for child and mother shall be automatically linked to this unique ID where appropriate. Country and site codes shall also be assigned by the data management centre.

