#### 5.1.2 Primary study outcome 2: Applicability of GAIA case definitions

Sample size estimations for these outcomes are provided as an indication of the precision level that can be achieved, depending on the number of cases identified per health outcome per site during the study period.

Table 1 shows the number of cases required for different levels of precision and expected proportions of applicability.

*Table 1. Number of cases required for different levels of precision*

| Relative precision | Expected proportions (applicability) |     |     |
|--------------------|--------------------------------------|-----|-----|
|                    | 20%                                  | 50% | 80% |
| 10% (+/- 5%)       | 246                                  | 384 | 246 |
| 20% (+/- 10%)      | 62                                   | 97  | 62  |
| 30% (+/- 15%)      | 28                                   | 43  | 28  |
| 40% (+/- 20%)      | 16                                   | 25  | 16  |

Assuming proportions of 50% ('worst case'), 97 cases would enable the calculation of proportions with 20% relative precision.

In the analysis, proportions for the primary analysis will be calculated overall and stratified by site, country, region, health facility level of care. The smallest unit is the site. Therefore, 97 cases per outcome per site would be required for 20% precision around proportions of 50%.

For this reason, we aim to enroll 100 cases per outcome per site. Failure to achieve the target of 100 for some outcomes and sites due to a low occurrence of the outcome under study will result in a loss of precision.

For some sites and outcomes, the number of subjects identified with the outcome of interest may exceed 100 during the study period. At each site, cases with outcomes of interest will be consecutively recruited into the study, until 100 cases for each outcome have been recruited, or the end of the study period is reached, whichever occurs first.

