## 5.2.2 Primary study outcome 2: Applicability of GAIA case definition

### 5.2.2.1 Health outcomes

For each health outcome, applicability of GAIA case definition will be assessed by calculating the proportion of cases identified that can be classified according to the GAIA case definition.

The denominator will be the number of cases identified for which the CRF was completed for one health outcome; the numerator will be the number of cases identified for that health outcome that can be classified according to the GAIA case definition.

The applicability of the GAIA case definitions for each health outcome will be reported overall, and stratified by site/country/region, and by health facility level (primary/secondary/tertiary).

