### 5.3.1.2 *Exposure to vaccination*

For the exposure to maternal vaccination, the proportion of maternal vaccinations that can be classified according to each GAIA exposure definition level will be assessed.

*Proportion of vaccinated mothers identified classified by level*

- The proportion of maternal vaccinations identified that can be classified according to each GAIA definition level will be assessed.
- The denominator will be the number of *identified* maternal vaccinations; the numerator will be the number maternal vaccinations classified for each level of the GAIA definition.

*Proportion of cases classified by level*

- The proportion of vaccinated mothers classified by level will be calculated.
- The denominator will be the number of *classified* maternal vaccinations; the numerator will be the number of maternal vaccinations classified for each level of the GAIA definition.

These proportions will be reported overall, and stratified by country/region, and by health facility level (primary/secondary/tertiary).

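### Section 5.3.1.1 divides the level-by-level proportions by all identified cases, although only cases with a completed CRF can be classified and the primary analysis divides by those

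*Protocol*

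**What the plan says.** **Primary (5.2.2.1).** Applicability is classified cases over a restricted set: "The denominator will be the number of cases identified for which the CRF was completed for one health outcome".

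**Secondary (5.3.1.1).** Two sets of level proportions are planned. For the first, "the proportion of cases identified that can be classified according to each GAIA case definition level will be assessed". Its denominator is the number of cases identified for the outcome, with no mention of the CRF. The second set divides by classified cases. Both are reported overall, by site, country and region, and by facility level.

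**What identified means.** Section 4.7: "Identified cases are defined as children delivered at the site with a diagnosis of one of the health outcomes of interest at the same site". Section 4.9 takes the count from the register of all deliveries: "the total number of live births over one year and the total number of cases identified among those delivered at the site will be derived".

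**Who has a CRF.** Under 4.9 an infant enters the study only once the eligibility criteria, including consent, are met. Recruitment at each site runs "until 100 cases for each outcome have been recruited, or the end of the study period is reached, whichever occurs first". Case-ascertainment data are collected in the electronic CRF. Section 5.1.2 foresees that at some sites "the number of subjects identified with the outcome of interest may exceed 100 during the study period".

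**Factors (5.3.2).** The proportion of identified cases that can be classified is tabulated by factor and compared with a chi-square test. No denominator is stated.

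**Exposure.** In the primary analysis (5.2.2.2), "The denominator will be the number of vaccination mothers identified". In 5.3.1.2 the text moves between vaccinated mothers and vaccinations: "The proportion of maternal vaccinations identified that can be classified according to each GAIA definition level will be assessed".

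**The concern.** Numerator and denominator in 5.3.1.1 come from different sets. A case without a CRF, because it arose after the 100th recruit or because consent or the form is lacking, stays in the denominator but can never reach the numerator. The level proportions then mix two quantities: how well the definition can be applied, and what share of identified cases was sampled.

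The first is what the secondary objective asks about. The second depends on case volume, consent and form completion. Because the tables are broken down by site and facility level, a busy hospital could appear to classify fewer of its cases than a small one that applies the definition equally well. Section 5.3.2 repeats the same phrase and attaches a test to it, so the same mixture could produce a significant result with no difference in applicability.

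For exposure, 5.2.2.2 counts mothers while 5.3.1.2 defines its numerators and denominators as vaccinations. The maternal immunization CRF in Annex V allows several dose records per mother, so the unit has to be fixed.

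**Working it through.** **The plan's own figure.** The target of 100 rests on 97 cases per outcome per site in Table 1. With n = z²p(1−p)/d², z = 1.96, p = 0.50 and d = 0.10: 3.8416 × 0.25 / 0.01 = 96.04, rounded up to 97. The figure reproduces. The recruitment limit is therefore a precision target for classifying recruited cases, which fits the 5.2.2.1 denominator.

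**Notation, per site and outcome.** N = identified cases (4.7, 4.9); R = cases with a completed CRF, with R ≤ N and R ≤ 100 (4.9, 5.1.2); C = classified cases, the sum of C₁, C₂, … over levels.

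- Primary applicability (5.2.2.1): C/R.
- Sum of the level proportions as written (5.3.1.1): C₁/N + C₂/N + … = C/N = (C/R) × (R/N).

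The two agree only when R = N.

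**Above the cap.** The protocol gives neither site volumes nor an applicability figure, so C/R = 80% and the values of N are assumptions. With R = 100, C = 80:

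| N | Primary C/R | Level sum C/N | Ceiling R/N if every CRF case is classified |
|---|---|---|---|
| 100 | 80% | 80/100 = 80% | 100% |
| 150 | 80% | 80/150 = 53.3% | 66.7% |
| 200 | 80% | 80/200 = 40% | 50% |
| 500 | 80% | 80/500 = 16% | 20% |
| 1,000 | 80% | 80/1,000 = 8% | 10% |

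**Below the cap.** If consent or forms are missing so that R/N = 90%, 80% or 70% (assumed), the sum is 0.80 × 0.90 = 72%, 0.80 × 0.80 = 64% or 0.80 × 0.70 = 56%.

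**Section 5.3.2, if it takes the same denominator.** Take two categories of one site each, both classifying 80 of 100 CRF cases, with 100 and 200 identified. The proportions are 80/100 and 80/200. The pooled proportion is 160/300 = 0.533, and chi-square = 0.40² / [0.533 × 0.467 × (1/100 + 1/200)] = 0.16/0.003733 = 42.9, p = 6 × 10⁻¹¹. With CRF denominators both are 80/100 and chi-square is 0.

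**With one denominator.** If the 80 classified cases split 40, 25 and 15 by level (assumed), dividing by R gives 40% + 25% + 15% = 80%, equal to the primary, whether N is 100, 200 or 500.

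**Unaffected measure.** The second set in 5.3.1.1 gives 40/80 = 50%, 25/80 = 31.2% and 15/80 = 18.8%, whatever N is.

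**Exposure.** If doses were the unit, a mother with two recorded doses would enter numerator and denominator twice. That changes the weights; it does not lower the proportion in the way that R/N does.

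**The case against.** The best defence is that 5.3.1.1 is shorthand. Section 5.2.2.1 also opens by speaking of identified cases and only then narrows the denominator. Section 4.10 says that identified cases will be classified, which is possible only where the data exist. The emphasis on the word in 5.3.1.1 sets it against classified cases, not against cases with a CRF. The authors may well have meant the same set in both places. That is plausible, but the protocol does not say it, 4.7 defines the term otherwise, and 4.9 derives a count that fits the wider definition. A protocol that states a denominator should state the intended one.

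Three stronger readings are tempting, and the documents do not support them.

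- *The primary and secondary results cannot be reconciled.* They differ by the factor R/N. Both counts are collected, so either result can be rescaled to the other, and no information is lost.
- *Sites below 100 cases escape.* They do so only if every identified case has a completed CRF. Consent is an entry condition, so a gap can open at any volume.
- *Counting vaccinations deflates the exposure proportions and distorts site comparisons.* Doses would enter both parts of the fraction, and 5.3.1.2 lists country, region and facility level as strata, not site. The wording there also shifts between mothers and vaccinations, so loose drafting is as likely as a deliberate change of unit.

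It is also fair that the measure is secondary and descriptive and that its true size cannot be known from the protocol.

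**Conclusion.** The point holds on the text as written and is moderate. Section 5.3.1.1 uses a wider denominator than 5.2.2.1, and its level proportions are multiplied by CRF-completed/identified. The factor is 1 only where every identified case has a completed CRF. The percentages above rest on an assumed 80% applicability and assumed volumes and completion rates. What does not depend on the 80% is that with N identified cases and at most 100 CRFs the sum cannot exceed 100/N, even with perfect classification.

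The primary applicability result and the proportions among classified cases stand. Section 5.3.2 carries the same ambiguity into a significance test, which makes it at least as important to settle. The exposure part is a smaller matter: an inconsistency of unit between 5.2.2.2 and 5.3.1.2 that affects weighting.

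**What to change.** - **5.3.1.1:** for the first set of level proportions, adopt the denominator of 5.2.2.1, that is, identified cases with a completed CRF for the outcome.
- **5.3.2:** state that same denominator for the tabulation and the chi-square test.
- **Reporting:** give the numbers identified, recruited and CRF-completed by site and outcome, with CRF-completed/identified shown separately as the sampling fraction.
- **5.3.1.2:** use the mother as the unit, as in 5.2.2.2, and label any dose-level results supplementary. How a mother with several doses is assigned a level is for the study team to define.

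The cost is a few sentences of wording. No new data are needed, because the register and the CRFs already supply every count.

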### 5.3.1.2 *Exposure to vaccination*

For the exposure to maternal vaccination, the proportion of maternal vaccinations that can be classified according to each GAIA exposure definition level will be assessed.

*Proportion of vaccinated mothers identified classified by level*

- The proportion of maternal vaccinations identified that can be classified according to each GAIA definition level will be assessed.
- The denominator will be the number of *identified* maternal vaccinations; the numerator will be the number maternal vaccinations classified for each level of the GAIA definition.

*Proportion of cases classified by level*

- The proportion of vaccinated mothers classified by level will be calculated.
- The denominator will be the number of *classified* maternal vaccinations; the numerator will be the number of maternal vaccinations classified for each level of the GAIA definition.

These proportions will be reported overall, and stratified by country/region, and by health facility level (primary/secondary/tertiary).

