#### 4.7.8 Ascertainment of vaccine exposure

To assess whether sites are able to determine whether a vaccine had been administered during pregnancy or within 30 days prior to the last menstrual period (LMP). Maternal vaccination status for tetanus or any other vaccines administered during pregnancy will be ascertained for all mothers of identified cases with the health outcome of interest.

A mother who has any mention of maternal vaccination will be considered vaccinated (exposed). This could be a formal recording of vaccination or any other mention in the documents available to the sites.

A mother who has documented evidence of absence of maternal vaccination will be considered non-vaccinated (non-exposed).

Any mother without any indication will be considered to have exposure status 'unknown'.

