## **Maternal immunization**

### Level 1 of diagnostic certainty

1. Woman confirmed as pregnant by positive pregnancy test or ultrasound confirmation

AND

2. Date/time of immunization of pregnant woman recorded in medical records by health care worker who administered/witnessed administration of vaccine

AND

3. Details of vaccine, including lot number, date of immunization

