### Maternal immunization

| QUESTION                                                                                  |                                                                                                                                                                                    | ANSWERS                                  |
|-------------------------------------------------------------------------------------------|------------------------------------------------------------------------------------------------------------------------------------------------------------------------------------|------------------------------------------|
| 1                                                                                         | What is the date of LMP ?
(if 'unknown', skip all questions on 30 days before LMP)                                                                                              | Please enter DDMMYYYY or unknown. |
| 2a                                                                                        | Did the mother receive any vaccination during pregnancy?
Please only answer 'no' if there is documented evidence of no immunization; else please answer 'unknown'.       | Yes
No
Unknown                     |
| 2b                                                                                        | Did the mother receive any vaccination in the 30 days before LMP? Please only answer 'no' if there is documented evidence of no immunization; else please answer 'unknown'. | Yes
No
Unknown                     |
| (If the answer to both question above is 'no' or 'unknown', end of questionnaire.) |                                                                                                                                                                                    |                                          |
| 3                                                                                         | How many vaccine doses were administered during pregnancy in total?                                                                                                                | 1
2
3
4
>4
Unknown        |

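### Maternal immunisation is counted per mother in the primary applicability result but per vaccination in the by-level results that claim to describe mothers, so the two need not agree

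*Protocol*

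**What the plan says.** Section 5.2.2.2 of the protocol, a primary outcome, is per mother throughout. "The denominator will be the number of vaccination mothers identified", and "the numerator will be the number of vaccination mothers identified that can be classified according to the GAIA definition".

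Section 5.3.1.2, the corresponding secondary outcome, has two parts. The first is headed "Proportion of vaccinated mothers identified classified by level", yet its denominator is identified maternal vaccinations and "the numerator will be the number maternal vaccinations classified for each level of the GAIA definition". The second states its target as "The proportion of vaccinated mothers classified by level will be calculated", and then again divides vaccinations by vaccinations. The sub-heading over that second part speaks of cases, although the section is about exposure.

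The maternal immunization CRF in Annex V asks "How many vaccine doses were administered during pregnancy in total", with answers from 1 to more than 4. For each dose it then repeats the items on disease, source of information, date, recorder and lot number. Doses in the 30 days before the last menstrual period (LMP) have their own question, count and dose records.

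Section 4.7.8 opens with the sites' ability to find out whether a vaccine was "administered during pregnancy or within 30 days prior to the last menstrual period (LMP". Its next sentence limits the status to vaccines given in pregnancy, as does section 4.5. In Annex III all three levels concern a pregnant woman or vaccination in pregnancy; Level 1, for example, requires "Date/time of immunization of pregnant woman recorded in medical records by health care worker".

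**The concern.** A by-level table should break down the primary result: the shares of those identified, summed over levels, should return the proportion that can be classified. That holds only if both use the same unit. Here the formula in 5.3.1.2 conflicts with 5.2.2.2 and also with its own heading and stated target. An analyst cannot follow both the target and the formula.

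The difference can be real because the CRF lets the units diverge. A mother with two tetanus doses is one unit in the primary result and two in the by-level result. If one dose is documented on a card and the other only reported by her, she appears at two levels. Section 5.2.2.2 is also incomplete for her, since nothing says whether a mother is classified when only some of her doses are.

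Applicability of this definition is a primary objective and the level distribution a secondary one, and both are to be compared between countries, regions and facility levels. Dose weighting could shift those comparisons wherever the number of recorded doses per mother differs.

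A smaller question concerns doses before LMP. They are collected under exposure ascertainment, the rule for calling a mother exposed has no time window, and no GAIA level can accommodate such a dose. Whether a mother with only such a dose enters the denominator is left unclear.

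**Working it through.** The protocol gives no count of mothers, doses or pre-LMP doses, so there is no stated figure to reproduce. The check compares the definitions and then illustrates with assumed numbers.

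**1. Units as written**

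| Place | Stated target | Unit in the formula |
|---|---|---|
| 5.2.2.2 | mothers | mothers / mothers |
| 5.3.1.2, first part | mothers (sub-heading) | vaccinations / vaccinations |
| 5.3.1.2, second part | mothers (target sentence) | vaccinations / vaccinations |
| Annex V, maternal immunization CRF | – | one record per dose |

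**2. Shift between levels.** Assume 100 vaccinated mothers: 60 with two Level 1 doses and 40 with one Level 3 dose.
- By mother: Level 1 = 60/100 = 60%; Level 3 = 40/100 = 40%.
- By vaccination: 60 × 2 = 120 Level 1 doses and 40 × 1 = 40 Level 3 doses, so Level 1 = 120/160 = 75% and Level 3 = 40/160 = 25%.

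Every mother and every dose is classified here, so both columns sum to 100%. The example shows a shift between levels and nothing about summing to the primary result.

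**3. Failure to sum.** Assume that half of the mothers have one dose and half have two, and that each dose is independently classifiable with probability c.
- Per vaccination (the sum over levels in 5.3.1.2): (0.5 × c + 0.5 × 2c) / (0.5 + 0.5 × 2) = c.
- Per mother, any dose classified: 0.5c + 0.5[1 − (1 − c)²].
- Per mother, all doses classified: 0.5c + 0.5c².

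| c | Per vaccination | Per mother, any dose | Per mother, all doses |
|---|---|---|---|
| 0.50 | 50.0% | 62.5% | 37.5% |
| 0.80 | 80.0% | 88.0% | 72.0% |

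With c = 0.50 and the share of two-dose mothers running from 0 to 100%, the per-vaccination figure stays at 50%. The per-mother figure runs from 50% to 75% (any dose) or from 50% down to 25% (all doses). With no two-dose mothers the three coincide. The gap between the last two columns shows that 5.2.2.2 needs a rule for several doses as well.

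**4. Doses before LMP.** If a fraction f of the mothers counted as vaccinated had only a pre-LMP dose, none of them could be classified, and a true applicability p among the rest would read p(1 − f). For p = 80%:
- f = 2%: 0.80 × 0.98 = 78.4%
- f = 5%: 0.80 × 0.95 = 76.0%
- f = 10%: 0.80 × 0.90 = 72.0%

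The loss is p percentage points for each 1% of such mothers, that is 0.8 points at p = 80%. It arises only if these mothers are counted, which the protocol does not say.

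**The case against.** The strongest reply is that this is loose wording. Neither 5.2.2.2 nor 5.3.1.2 mentions doses, no passage says that each dose is classified separately, and 4.7.8 assigns vaccination status per mother. The authors may simply have written vaccinations for vaccinated mothers. The results are descriptive, the per-dose records allow either unit to be derived, and a rule for several doses could be left to the statistical analysis plan, which is not at hand.

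Much of that stands. It rules out saying that the results cannot be reconciled; they need not agree as written, and they do agree if every mother has one dose. It also rules out saying that the authors intended a dose-level analysis. It does not remove the conflict. The protocol itself fixes numerators and denominators in 5.3.1.2, and they contradict both the stated target and the primary definition. A later plan would have to depart from one of them.

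On doses before LMP, a reader might infer that they count as exposure and so depress applicability by construction, most of all at sites with good LMP records, because the CRF skips those items when LMP is unknown. The documents do not support this. The 30-day window stands in a sentence on site capacity, the next sentence and section 4.5 point to pregnancy only, and the CRF keeps these doses apart so that they can be left out. What remains is an ambiguity.

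**Conclusion.** The inconsistency of unit is established from the text: mothers in 5.2.2.2, vaccinations in the formulas of 5.3.1.2, and mothers again in that section's heading and target. Taken literally, the by-level shares are dose-weighted, can place one mother at two levels, and need not add up to the primary proportion.

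The size is unknown because the protocol gives no dose counts. Under the assumed numbers, the Level 1 share moves from 60% to 75%, and classifiability of 50% per vaccination corresponds to 62.5% or 37.5% per mother depending on the rule for several doses. The second illustration rests on half of the mothers having two doses and on independence between doses. A reader might also infer that dose weighting favours women with better antenatal documentation; that is plausible, but nothing in the protocol shows it.

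The handling of mothers with only a pre-LMP dose is ambiguous. If they were counted, applicability would read p(1 − f); whether they are counted is not stated. The whole point is worth correcting, but it is a matter of definition and does not damage the data collected.

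**What to change.** - In 5.3.1.2, make the mother the unit in every numerator and denominator, as in 5.2.2.2, and correct the second sub-heading to match.
- State one rule for a mother with several doses and apply it in both sections. An example is the highest level reached by any dose given during pregnancy; another rule would serve if it is stated beforehand.
- If a per-vaccination breakdown is wanted, give it as a supplementary table labelled as such.
- In 4.7.8, 5.2.2.2 and 5.3.1.2, align the denominator with section 4.5 (mothers with at least one vaccine during pregnancy) and report mothers with only a pre-LMP dose on a separate line.

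The cost is a few sentences. The data are already collected by dose and by time window, so the CRF does not change; the supplementary table is minor extra programming.
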